##### ✓ Recruitment

The investigators will jointly publicize this clinical trial recruitment notice to qualified volunteers/guardians, examined, and approved by the Ethics Committee, with local medical staff, and recruit and register candidate subjects based on the principle of voluntary participation. During the study, the recruitment should be adjusted in real time progress, to ensure that the gender and age of the participants are relatively balanced

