## **4.6 Randomization and Blinding**

### **4.6.1 Randomization**

Stratified block randomization method will be employed in the study to perform stratifications according to sequential vaccination time (1-3 months, 4-6 months, and  $\geq 6$  months after 2 doses). Interactive Web Response System (IWRS) will be used in subject randomization and vaccine allocation.

The randomization statistician will produce subject randomization list and vaccine randomization list by SAS 9.4 (or later version), which will be imported into IWRS by system engineer. After one subject is screened successfully, the investigator at each center will log onto IWRS to get randomization number of the subject. Before vaccination, the investigator will receive the vaccine number from IWRS and inoculate vaccines accordingly. If the vaccine is damaged, the investigator could acquire a new vaccine number from IWRS and inoculate the vaccine with new vaccine number.

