### **10.3.2 Subject Disposition**

The number of subjects who are enrolled, completed and discontinued will be summarized in each group. The reason for discontinuation will be analyzed as well.

The demographic characteristics will be summarized and described by treatment group.

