### **10.3.3 Immunogenicity Analysis**

ANCOVA model will be employed to analyze post-vaccination GMT. In the model, log-transformed GMT after vaccination will be included as dependent variable, pre-vaccination GMT after log-transformation is the covariate and group assignment and sequential vaccination time (1-3 months, 4-6 months and  $\geq 6$  months after the sequential dose) are the fixed effect. The adjusted LSMean in each arm and difference between the two groups together with 95% confidence interval (CI) will be estimated from the model. After inverse log-transformation, the adjusted GMT after vaccination and GMT ratio together with 95% CI between treatment and control groups will be derived. If the lower bound of 95%CI is larger than 0.67, the non-inferiority result will be concluded.

The 4-fold rise, and the proportions of antibody titered  $\geq 1:16$ ,  $\geq 1:32$  and  $\geq 1:64$  after vaccination in both vaccine and placebo groups will be estimated. The corresponding 95% CIs will be derived from Clopper-Pearson method. The difference between the two groups and their 95% CIs will be estimated by CMH method including the stratification factor (sequential vaccination time). If the lower bound of 95%CI in 4-fold rise rate is larger

than -10%, the non-inferiority will be concluded.

The descriptive statistics, including geometric mean and corresponding 95% CI, are employed to summarize GMT and GMI after sequential dose. The t-tests after log transformation will be compared between the two groups.

The reverse cumulative distribution plot is to depict the pre- and post-vaccination antibody data in the vaccine and placebo groups.

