### **12.2. Source Data and Subject Files**

Source documents provide evidence for the existence of the subject and substantiate the integrity of the data collected. Source documents are filed at the investigator's site.

The investigator has to keep a written or electronic subject file for every subject

participating in the clinical study. In this subject file, the available demographic and medical information of a subject has to be documented, in particular the following: name, date of birth, sex, height, weight, statement of entry into the study, study identification, randomization number, the date of informed consent, all study visit dates, predefined performed examinations and clinical findings, observed AEs, and reason for withdrawal from the study, if applicable.

It should be possible to verify the inclusion and exclusion criteria defined in the protocol from the available data in this file.

It must be possible to identify each subject by using this subject file. Additionally, any other documents with source data, especially original printouts of data that were generated by technical equipment have to be filed. This includes but not limited to ECG tracings, X-ray films, CT and MRI scans, laboratory value listings and QoL questionnaires, etc. All these documents have to bear at least the subject identifier and the printing date printed by the recording device to indicate to which subject and to which study procedure the document belongs. The medical evaluation of such records should be documented as necessary and signed/dated by the investigator.

Computerized subject files will be printed whenever source data verification is performed by the monitor. Printouts must be signed and dated by the investigator, countersigned by the monitor and kept in a safe place.

Data entered in the eCRFs that are transcribed from source documents must be consistent with the source documents or the discrepancies must be explained. The investigator may need to request previous medical records or transfer records, depending on the case; also, current medical records must be available.

Data on the subject dairies are considered source data and have to be stored along with the subject file. The data of the dairies will be forwarded to the sponsor or a CRO appointed by the sponsor for data entry into the data base.

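### The GMT ANCOVA omits age and sex, both recorded at baseline; prespecifying them as covariates would be a near-free, small gain in precision, chiefly within the interval cohorts.

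*Protocol*

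**What the plan says.** - **GMT model.** Section 10.3.3 states that "pre-vaccination GMT after log-transformation is the covariate and group assignment and sequential vaccination time" are the fixed effects. No other term is named.
- **Four-fold rise.** The same section has the difference between groups "estimated by CMH method including the stratification factor (sequential vaccination time"), again without age or sex.
- **Randomisation.** Section 4.6.1: "Stratified block randomization method will be employed in the study to perform stratifications according to sequential vaccination time". Allocation is central, through the IWRS. The interval since the second dose is the only stratum.
- **Recruitment.** Under Recruitment in 7.2.1, enrolment is adjusted as it proceeds "to ensure that the gender and age of the participants are relatively balanced".
- **Availability of the data.** Table 4 has demographics collected at V1. Section 12.2 lists "name, date of birth, sex, height, weight, statement of entry into the study" among the contents of the subject file. Section 5.1.1 admits anyone aged 18 or over, with no upper limit.
- **Use of the data.** Section 10.3.2: "The demographic characteristics will be summarized and described by treatment group". No inferential analysis in section 10 uses age or sex.

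**The concern.** The protocol pays attention to age and sex when it enrols people and then makes no inferential use of them. If either predicts the post-vaccination titre beyond what the baseline titre predicts, that variance stays in the residual and widens the confidence interval of the GMT ratio. In a population open to all adults some such effect is plausible, though the documents do not quantify one.

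The interval matters because non-inferiority is judged on its lower bound. In the pooled comparison there is ample room. Within a cohort there is little: section 10.1 derives 300 per arm per cohort from a requirement of 250 plus drop-out, and section 10.4 repeats the immunogenicity analysis in each cohort.

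Section 10.3.3 lists the model terms explicitly. A statistical analysis plan could add a supplementary adjusted analysis, but changing the main model there would depart from the protocol. The covariates are best settled in the protocol, before unblinding.

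**Working it through.** **Inputs from the protocol (10.1, 4.4).** One-sided alpha 2.5% (z = 1.960); power 80% (z = 0.842); GMT ratio margin 2/3, so d = log10(1.5) = 0.1761; SD of log10 titre 0.7; equal true GMTs; 300 per arm per cohort and 900 per arm overall; drop-out 15% to 20%.

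**Assumed input.** R², the share of residual log-titre variance that age and sex explain: 1% to 10%. The SD of 0.7 is treated as the residual SD of the model as it stands.

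**Step 1: the plan's own figure.** n per arm = 2 × SD² × (1.960 + 0.842)² / d² = 2 × 0.49 × 7.849 / 0.03101 = 248.1, so 249. The noncentral t calculation gives 250, the figure in 10.1.

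**Step 2: what drop-out leaves.** 250/0.85 gives 295 and 250/0.80 gives 313, against 300 planned. At 20% drop-out, 300 × 0.80 = 240 remain per arm in a cohort and 900 × 0.80 = 720 overall.

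**Step 3: effect of the two covariates.** Residual SD = 0.7 × √(1 − R²). Required n = 248.1 × (1 − R²), rounded up. Power = Φ(d / (SD × √(2/n)) − 1.960).

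| R² (assumed) | SD | n per arm for 80% | Power, cohort (240 per arm) | Power, pooled (720 per arm) |
|---|---|---|---|---|
| 0 | 0.700 | 249 | 78.7% | 99.75% |
| 1% | 0.697 | 246 | 79.1% | 99.77% |
| 5% | 0.682 | 236 | 80.7% | 99.83% |
| 10% | 0.664 | 224 | 82.8% | 99.89% |

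For example, at R² = 5% and 240 per arm: 0.1761 / (0.682 × √(2/240)) − 1.960 = 0.867, and Φ(0.867) = 80.7%.

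**Step 4: cost.** Two further parameters raise the standard error by roughly √(477/475) = 1.002 in a cohort of 480 and √(1435/1433) = 1.0007 in the pooled set of 1,440. In a cohort the change breaks even at R² of about 1 − 475/477 = 0.4%. Below that there is a loss of at most about 0.2% in the standard error.

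**Step 5: validity of the model as written.** In simulations of 20,000 trials at 250 per arm, with a baseline covariate explaining 5% or 10% of variance, type I error at the margin was 2.5% to 2.6% without adjustment and 2.5% with it. Power went from 80.8% to 82.7% at 5%, and from 80.5% to 84.4% at 10%.

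**Step 6: size of chance imbalance.** With half the subjects of each sex, the 95% range of the difference in proportions between arms is 1.96 × √(0.25 × 2/n). This is ±4.6 points at 900 per arm and ±8.0 points at 300. If sex shifted log10 titre by 0.1 (assumed), an imbalance at that limit would move the GMT ratio by a factor of 10^0.0046 = 1.011, or 10^0.0080 = 1.019. The margin allows a 33% reduction.

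**The case against.** The strongest case on the other side is that nothing here is wrong. Randomisation balances age and sex in expectation, the listed model adjusts for the baseline titre and the stratification factor, and its type I error is nominal. The pooled model gains almost nothing, the cohort analyses are labelled subgroup analyses, and the R² is assumed. All of this stands, and it limits the point to a suggestion.

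A reader might also infer that the Recruitment paragraph promises balance between arms, which steering enrolment under central blinded allocation could not deliver. The text does not support that reading. It speaks of the participants, not of groups, and it describes a stage before randomisation. Its natural meaning is the age and sex mix of the enrolled sample, which recruitment can influence.

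A further objection is that adjusting only the ANCOVA leaves it with different covariates from the four-fold-rise analysis, although section 10.6 requires both to succeed. They differ already: the ANCOVA carries the baseline titre and the CMH analysis does not. Extending the change to the strata or the CMH analysis would not be free, because crossing three intervals with sex and age groups makes smaller cells.

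**Conclusion.** The point holds as a small improvement in precision. It does not show an error, a bias or a contradiction in the protocol.

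The benefit is negligible for the pooled GMT comparison. Within a cohort at the protocol's upper drop-out figure, it is about two percentage points of power at R² = 5%, enough to move 78.7% just above the 80% target. At R² = 1% it is less than half a point and the target is still missed.

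This rests on an R² that the documents do not supply. Part of any age or sex effect may already be carried by the baseline titre, which would put the true value towards the lower end. If the residual SD after baseline adjustment is below 0.7, cohort power is already higher than shown and there is less to gain.

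**What to change.** In section 10.3.3, add age (continuous, in years) and sex to the terms of the GMT ANCOVA, and state that the same covariates apply in the per-cohort analyses of section 10.4. Leave the randomisation strata and the CMH analysis as they are.

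The cost is one sentence in the protocol and two degrees of freedom. No new data are needed, and the sample size and the non-inferiority criteria do not change. The amendment should be made before unblinding.

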##### ✓ Informed Consent

Informed consent refers to the voluntary participation of subjects in clinical studies. Prior to the commencement of any test-related procedures (any genetics-related sample collection, testing, etc.), a written informed consent must be obtained from the subject.

After arriving at the research site, the subjects first give informed consent. The investigators inform the subjects of the informed consent form of this clinical trial orally and in writing, including study purpose, procedure, duration, risks and benefits, etc. Under the condition of voluntary participation, the subjects and research doctors signed an informed consent form together. The informed consent form shall be made in duplicate, and the guardian or principal of the volunteer shall keep a copy, and the original shall be kept at the study site.

Collect contact information (address, e-mail, landline, and mobile phone numbers, etc., if applicable) of subjects and their families.

##### ✓ Physical Examination, Inclusion/Exclusion Criteria

Volunteers who signed the informed consent were given height, weight, body temperature, blood pressure (aged 18 and above), cardiopulmonary auscultation, skin examination. Within 10 minutes before the temperature test, the subjects are forbidden to eat or drink anything hot or cold, or smoke.

According to the "inclusion criteria" and "exclusion criteria", the investigators inquire, understand, and check the vaccination records of the subjects, that is, the past medical history, and

judged whether the subjects should be enrolled in this clinical trial according to the inquiry results.

✓ **Study Number Assignment**

Eligible subjects are assigned unique study numbers in sequence. Once the study number is assigned, it cannot be reassigned to other subjects.

✓ **Blood Sample Collection before Vaccination**

Women of childbearing age (from menarche to menopause) need to collect about 2ml urine samples for urine pregnancy test before vaccination.

About 12.5 ml of blood samples are collected on an empty stomach for SARS-CoV-2 antibody detection after recruitment.

Nasopharyngeal swabs are collected for PCR detection to establish antibody baseline and PCR baseline for booster inoculation. After sample collection, the subjects can enter the following process.

✓ **Vaccination**

Subjects can be vaccinated after sample collection. Before vaccination, it is necessary to check the information of subjects and the investigational vaccines, obtain vaccines with corresponding numbers and open the outer package. After the vaccine label and outer package label are checked, fill in the initials of the vaccinee's name and vaccination date on the label of the outer package.

Vaccination site is at the lateral deltoid muscle of upper arm, in principle, the non-habitual arm of the subject.

During vaccination, the investigational vaccine and control vaccine should be kept at 2 ~ 8 °C (the temperature should be monitored and recorded every 1 hour), and it should take no more than 30 minutes from the time the vaccine is taken out of the heat preservation container to the completion of vaccination.

During vaccination, in case of abnormal color, damage, insufficient loading or precipitation, it is necessary to stop vaccination immediately, report to the sponsor, auditor and on-site person in charge, discard the original vaccine according to the procedure after confirming the damage of the vaccine, and obtain a new vaccine number in the system by the distribution principle of the central randomized system after approval.

Record the injection site (right arm or left arm) and vaccination information.

### ✓ **On-site Medical Observation**

Observe the immediate adverse reactions 30 minutes after vaccination. Doctors explain on-site adverse reaction judgment, measurement methods, recording methods, precautions, reporting methods, etc. Diary cards, rulers and thermometers are distributed and train subjects how to use thermometers correctly, observe adverse events and fill in diary cards within 0-7 days after vaccination, and inform them of the time to make an appointment to return the diary cards (return the completed diary cards on Day 14 Visit 4 ).

Ask the subjects to try to take temperature measurements at the same time every day within 7 days after vaccination.

Before leaving the study site, the vaccination site and body temperature of the subjects should be checked, and the observed adverse events should be evaluated and recorded in the electronic system.

Inform the subjects that they should take the initiative to provide any adverse reactions and accompanying medication. If there is any reaction after vaccination, it is necessary to inform the study center in time. PI or qualified SI will evaluate them, provide the subjects with correct response plan, and ask them to return to the clinic for immediate evaluation if necessary

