**Safety endpoint:**

The incidence and severity of any adverse reactions/events within 30 minutes after vaccination;

The incidence and severity of solicited adverse reactions/events within 0-7 days after vaccination;

The incidence and severity of unsolicited adverse reactions/events within 8-30 days after vaccination;

The incidence of SAE and AESI observed after vaccination and up to 6 months after full course of immunization.

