| Rash *, flush * * # | 2.5 ~ < 5 cm in diameter or 6.25 ~ < 25 cm  in area not or slightly affecting daily life | 5 ~ < 10 cm in diameter or 25 ~ < 100 cm  in area or affecting daily life | Diameter ≥ 10 cm or area ≥ 100 cm  or ulceration or secondary infection or phlebitis or sterile abscess or wound drainage or serious affect daily life | Abscess, exfoliative dermatitis, dermal or deep tissue necrosis |
| Pruritus            | Itching at the vaccination site was relieved by itself or within 48 hours after treatment            | Itching at the vaccination site did not relieve within 48 hours after treatment       | Affect daily life                                                                                                                                                  | NA                                                              |

Note: \* In addition to measuring the diameter directly for grading evaluation, the progress and change of measurement results should also be recorded.

\*\* Maximum measured diameter or area shall be used.

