**Table 3 Systemic Adverse Events Grading Table**

| Physical Sign                     | Grade 1                                                                                                       | Grade 2                                                                                       | Grade 3                                                                          | Grade 4                                      |
|-----------------------------------|---------------------------------------------------------------------------------------------------------------|-----------------------------------------------------------------------------------------------|----------------------------------------------------------------------------------|----------------------------------------------|
| Fever * (axillary temperature °C) | 37.3 ~ < 38.0                                                                                                 | 38.0 ~ < 38.5                                                                                 | 38.5 ~ < 39.5                                                                    | ≥ 39.5 for more than 3 days                  |
| Diarrhea                          | Mild or transient, 3 ~ 4 times/day, abnormal fecal characteristics, or mild diarrhea lasting less than 1 week | Moderate or persistent, 5 ~ 7 times/day, abnormal fecal characteristics, or diarrhea > 1 week | > 7 times/day, abnormal fecal characteristics, hemorrhagic diarrhea, orthostatic | Hypotensive shock, requiring hospitalization |

|                 |                                                               |                                                                                                           |                                                                                                   |                                                                               |
|-----------------|---------------------------------------------------------------|-----------------------------------------------------------------------------------------------------------|---------------------------------------------------------------------------------------------------|-------------------------------------------------------------------------------|

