## **7.3 Safety Observation and Follow-up**

### **7.3.1 Safety Observation**

(1) Observe the site for 30 minutes after vaccination to collect local and systemic adverse events.

(2) Telephone follow-up once in 6-24 hours after vaccination, within 1-3 days and 4-7 days respectively, the subjects were followed-up by telephone and guided to observe the adverse events

correctly and fill in the diary card.

(3) On the 14th day (Visit 4), the investigator reviews the filling of the diary card during this period and re-collect the diary card.

(4) On the 8th -30th day after vaccination, the investigator uses telephone follow-up once a week, combined with active report of the subjects to monitor the safety.

(5) When it is known that the subject has adverse reactions/events of Grade 3 or above, a face-to-face visit should take place within 24 hours.

(6) SAEs and AESIs are observed from the first dose to 6 months after the full course of vaccination by means of monthly telephone follow-up and self-reports from the subjects.

Note: Subjects should report respiratory tract infection symptoms such as fever and cough. Investigators should make comprehensive judgments, carefully identify whether it is common solicitation symptoms after vaccination or infection caused by other reasons, and closely observe the disease progress. Once the disease worsens, report it to the person in charge of the site quickly, and start the green treatment channel quickly to ensure that the subjects get timely diagnosis and treatment.

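### Home temperature on days 0-7 is scheduled as a fixed-time daily reading with no reading on symptoms and no daily maximum, so short fevers are liable to be missed or under-graded

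*Protocol*

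**What the plan says.** **Timing of readings.** Protocol Section 7.2.1, On-site Medical Observation: "Ask the subjects to try to take temperature measurements at the same time every day within 7 days after vaccination". Body temperature is also checked once before the subject leaves the site on the day of vaccination. No other section says when subjects take their temperature at home.

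**How fever is graded.** Section 4.5.1 lists fever among the systemic events collected on days 0-7. Table 3 (Section 4.5.2) grades it by axillary temperature: Grade 1 from 37.3 to below 38.0 °C, Grade 2 from 38.0 to below 38.5 °C, Grade 3 from 38.5 to below 39.5 °C. Grade 4 is 39.5 °C or more lasting over 3 days.

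**Which measurement counts.** For local reactions the note to Table 2 is explicit: "Maximum measured diameter or area shall be used". Table 3 has no such note for temperature.

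**Endpoint.** Synopsis, Safety endpoint: "The incidence and severity of solicited adverse reactions/events within 0-7 days after vaccination".

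**Other routes by which a fever may come to light.** Section 7.2.1 has staff "train subjects how to use thermometers correctly, observe adverse events and fill in diary cards within 0-7 days after vaccination". It also says "Inform the subjects that they should take the initiative to provide any adverse reactions and accompanying medication" and "If there is any reaction after vaccination, it is necessary to inform the study center in time". Section 7.3.1 adds "Telephone follow-up once in 6-24 hours after vaccination, within 1-3 days and 4-7 days respectively", and its closing note names fever among the symptoms to report. Section 7.2.2 has each call cover adverse events since the last contact.

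**The concern.** A reading at a set hour shows the temperature at that hour and not the day's peak. Fever is the one solicited event in Table 3 whose occurrence and lower grades rest on an instrument reading alone. If no reading is taken while the temperature is raised, there is no value from which to confirm or grade the event. If the scheduled reading falls on the way up or down, the event is recorded at too low a grade.

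What is at stake is the absolute frequency and severity of solicited fever in each arm, which the study reports as a safety endpoint. The loss would arise at data collection, so no later analysis could restore it.

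**Working it through.** The protocol gives no fever rate, fever duration or detection rate, so there is no figure of its own to reproduce. The check has two parts.

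**1. Grading, from Table 3 alone.** Band widths:

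- Grade 1: 38.0 − 37.3 = 0.7 °C
- Grade 2: 38.5 − 38.0 = 0.5 °C
- Grade 3: 39.5 − 38.5 = 1.0 °C

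A reading 0.5 °C below the peak puts any Grade 2 fever into Grade 1 (38.0 − 0.5 = 37.5; 38.5 − 0.5 = 38.0). A reading 0.7 °C below the peak takes any Grade 1 fever under 37.3 °C, so no event is recorded. A reading 1.0 °C below the peak turns any Grade 3 fever into Grade 1 or 2 (38.5 − 1.0 = 37.5; 39.5 − 1.0 = 38.5). The grade therefore depends on which reading is used, and the protocol names none for fever, whereas Table 2 names the maximum for lesion size.

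**2. Detection, as an illustration only.** Assumptions, none of them in the protocol: one fever episode of D hours starting at a random time, exactly one scheduled reading per 24 hours, and a share s of otherwise missed fevers caught because the subject measures or reports on symptoms.

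Detection = min(1, D/24) + [1 − min(1, D/24)] × s

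Example: D = 6, s = 0.5 gives 0.25 + 0.75 × 0.5 = 0.625.

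| D (hours) | s = 0 | s = 0.5 | s = 0.8 | s = 1 |
|---|---|---|---|---|
| 6 | 25% | 62.5% | 85% | 100% |
| 12 | 50% | 75% | 90% | 100% |
| 18 | 75% | 87.5% | 95% | 100% |
| 24 or more | 100% | 100% | 100% | 100% |

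A large loss needs both short fevers and s near zero. The reporting duties in Sections 7.2.1, 7.2.2 and 7.3.1 argue against s near zero, but the protocol does not fix s. The table covers detection only. A fever that is detected may still be graded below its peak, including one lasting 24 hours or more.

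**The case against.** The strongest reply is that the sentence in Section 7.2.1 sets a routine schedule and not a limit. It asks subjects to try to keep to one time, which reduces diurnal noise, and it does not forbid or discard other readings. A subject who feels feverish has a thermometer, has been trained to use it and is told to report reactions promptly. The telephone contacts are a further net. The diary card is not shown and may already ask for the day's highest temperature. All of this stands, and it is why no size can be given.

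It does not close the gap. Self-report and calls can establish that someone felt hot, but they cannot supply a temperature that nobody took, and Table 3 grades fever on a temperature. Calls at 6-24 hours and then within days 1-3 and 4-7 cannot recover an earlier peak.

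Three stronger readings are tempting, and the protocol does not support them:

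- **The fever endpoint is shown to be biased by a known amount.** Fever duration and the share caught on symptoms are not given, so only a liability can be stated.
- **The arm comparison is distorted or loses a stated amount of power.** The instruction is the same in both blinded arms. Under-capture would tend to shrink an absolute difference, but Section 10.1 sizes the study on immunogenicity only and no fever rates are given. No planned fever comparison has a power to lose.
- **The 15% suspension criterion is affected.** It counts subjects with any severe adverse reaction, and fever is one of many. Nothing in the protocol shows that missed fevers would change whether it is met.

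The contrast with Table 2 is also not a contradiction. It shows only that the protocol states a rule for one kind of measurement and leaves the other open.

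**Conclusion.** The point holds as a measurement rule that can be improved cheaply. The protocol fixes the routine home reading by clock time, does not ask for a reading on symptoms, and does not say that the daily maximum is recorded and graded. Short fevers between readings are therefore liable to be missed or under-graded in both arms, which would lower the absolute solicited-fever rate and its severity. The size is unknown. The illustrative range for a 6-hour fever, 25% to 100% detection, reflects the assumed duration and symptom capture and is not an estimate. The conclusion rests on Section 7.2.1 being the whole of the home measurement instruction. If the diary card already asks for symptom-triggered readings and the daily maximum, all that remains is to bring Section 7.2.1 into line with it.

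**What to change.** Keep the fixed-time reading in Section 7.2.1 as the daily minimum and add: *and whenever the subject feels feverish or unwell; the highest axillary temperature of each day (days 0-7) is recorded on the diary card and used for grading.* Add a field for the daily maximum to the diary card if it has none.

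The cost is one sentence and one field, since subjects already receive thermometers and diary cards. The downside is slightly more diary work and a less uniform number of readings per subject, under the same rule in both blinded arms. The change alters no grading threshold and no clinical rule.
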